**Fig. 2 Fig2:**

cRCT anticipated outcomes, data sources, and assumptions

### Recruitment {15}

Clusters will be included at a rate of ~2–3 per month per arm. Based on successes in the pilot study (6 Fokontany per month and community acceptability was high without TB-related stigma impeding activities), this enrolment rate is highly feasible.

## Assignment of interventions: allocation

Fokontany characteristics that were likely to be associated to the primary outcome of TB detection rates were identified as potential confounders. Based on results of a pilot study from the same rural area, those include (i) the baseline TB notification rate in the year prior the beginning of the trial, (ii) distance to the closest TB diagnostic and treatment center (CDT), (iii) population in each Fokontany, and (iv) closest TB care center. These continuous variables will be dichotomized using median measures for eligible Fokontany only. All these four factors will be included into the randomization algorithm, which will be done by minimization with equal treatment allocation [16, 25]. The allocation by minimization will decrease the risk of substantial imbalance in those important factors. The total imbalance for each treatment is calculated by summing the weighted imbalance scores across all prognostic factors [26]. The pre-specified covariate weights of 0.3, 0.3, 0.3, and 0.1 will be applied for baseline TB incidence, distance to CDT, Fokontany population, and closest TB care center covariates respectively. The weights were chosen based on the covariates’ distribution and potential clinical judgment. Fokontany will be randomized with an allocation ratio of 1:1:1 to assign 16 Fokontany clusters in each of arms 1, 2, and 3. Allocation by minimization with equal treatment allocation will be performed using R version 4.4.1.

### Sequence generation {16a}

Cluster allocation by minimization of 48 out of 145 Fokontany in arm 1, 2, or 3 will be performed by statistician prior the beginning of intervention. The covariates distribution by study arm will be reported. The intervention implementation order will be randomly and uniformly generated across quarters during the first year.

### Concealment mechanism {16b}

N/a: Concealment is not required since allocation will be performed randomly using statistical software.

### Implementation {16c}

Inclusion, stratification, and randomization will be overseen by a biostatistician. Field clinical teams will enroll participants.

## Assignment of interventions: blinding

### Who will be blinded {17a}

This will be an open-label trial. The potential undesired effect of the open-label design is that of patients seeking care in Fokontany randomized to different arms to access better diagnostic testing. With the “intention to treat” analysis, such detected cases would be recorded in their respective cluster and tend to reduce apparent impact of the novel intervention. Contamination between clusters is not expected because (i) rural Madagascar sociodemographic structure is such that populations are stable within their home Fokontany, (ii) a social network analysis (SNA) pilot study suggests almost absent interactions between persons from different Fokontany (pilot study), (iii) distance between clusters averages 6 km of twisting footpaths, and (iv) out of 145 Fokontany in the study area, 48 will be included.

### Procedure for unblinding if needed {17b}

N/a: as explained above, our study did not involve any blinding.

## Data collection and management

### Plans for assessment and collection of outcomes {18a}

TB case detection will be prospectively recorded in local CDTs. Data will be cross validated with both study records and NTP centrally aggregated data on a quarterly basis.

### Plans to promote participant retention and complete follow-up {18b}

Interventions will be implemented at healthcare system level; no participant retention or follow-up will be required.

### Data management {19}

Data collection and entry will be conducted by the study nurse. Data will be entered directly into a tablet and sent daily to the IPM server for storage. The data manager team will perform the data quality process, and data queries will be sent to the field team daily. All data will be stored on the IPM server, with a recovery system in place to protect against data loss. The main server is duplicated at a separate location. The study’s data manager will oversee the data management SOPs.

### Confidentiality {27}

All participants will be given a unique identifier (ID). Study results dissemination mechanisms will not allow for direct or indirect identification of patients. All information will be anonymized for downstream analyses including those which require inter-institutional data transfer between the investigators.

### Plans for collection, laboratory evaluation, and storage of biological specimens for genetic or molecular analysis in this trial/future use {33}

Clinical samples will be collected within communities during active case finding activities. Smear microscopy and Xpert MTB/RIF Ultra PCR testing will be performed at the Tambohobe regional hospital. Samples positive for TB will be referred to IPM reference laboratory for culture and WGS testing, results analysis, and reporting. Cultured bacterial strains will be stored at least 15 years at IPM. Primary clinical samples will not be stored.

## Statistical methods

### Statistical methods for primary and secondary outcomes {20a}

First, we will calculate TB case notification rates for each Fokontany. The overlapping TB cases resulting from our RCT study and from NTP report will be counted once in the outcome measures. The primary analysis will compare notification rates between arms after 1 year, using a simple *t*-test and nonparametric Mann–Whitney *U* test weighed by Fokontany size with Fokontany as the unit of analysis. Detection rate differences and 95% confidence intervals (CI) will be reported. The ICC will be calculated from the output of one-way analysis of variance (ANOVA) [27]. As a secondary analysis, the longer-term effect of sustained interventions will be evaluated for 2 years. The longitudinal impact of interventions will be evaluated with a linear mixed-effects model weighed by Fokontany size again conducted at the cluster level. The model will include the yearly TB detection rate, the study arm (1, 2, and 3), the year (first and second), and the interaction arm × year as the fixed effects and Fokontany as the random effect. The least squares mean estimates with 95%CI will be computed from the models. The longitudinal pattern of TB detection rate for each study arm and for each Fokontany will be presented graphically by 6- and 12-month interval. To estimate Fokontany size, we will use two approaches. First, we will consider primary data from the 2019 INSTAT-World Bank census (pilot study) with the 2.7% World Bank estimated annual increase [28, 29]. Then, we will consider the population reported by health authorities upon case finding visits. R software will be used for analyses.

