### Sample size {14}

This study will be powered to demonstrate superiority of arm 3 “novel intervention” over arm 2 “best practice” after 1 year. Given the purely incremental nature of arm 3 “novel intervention,” it is assumed it cannot be inferior. Using (i) realistic anticipated outcomes described below with 116% increase in TB case detection rate from 95/100,000/year to 206/100,000/year, (ii) Fokontany as the analysis unit, (iii) intraclass correlation coefficient (ICC) of 0.0005 for sample size adjustment, (iv) average Fokontany cluster size of 1800 inhabitants, and (v) assuming a one-sided *α* = 0.05 test with 80% power, we estimate the number of Fokontany in each arms should be 16 to allow detection of the TB detection rate difference using a simple *t*-test weighed by Fokontany size [23]. TB incidence data from every Fokontany in the Haute Matsiatra region were used to perform sample size calculation. Given the sufficient number of eligible Fokontany in the Vohibato district, 48 Fokontany from this district will be selected to increase feasibility and cluster homogeneity. Multiple simulations were performed to strengthen this sampling size strategy and are presented as Supplementary Materials 1. To estimate anticipated outcomes in each arm, to calculate the ICC and calculate sample size, we used (i) Madagascar TB incidence estimates from WHO, (ii) NTP data disaggregated by primary healthcare facility where services are similar to study interventions, (iii) a comprehensive and systematic baseline survey, and (iv) pilot studies assessing clusters interconnections and impact of arm 1 and arm 2 interventions (see Fig. 2) [11]. Using demographic, distance to healthcare facility, and baseline TB detection rates, the ICC was calculated to be 0.0005. This suggests homogeneity between clusters, which agrees with findings of social network studies performed in the same area and ICC values used in sub-Saharan African studies measuring TB case finding strategies in similar contexts [24]. For arm 1 “standard of care,” anticipated outcomes are adjusted to most reliable, contextualized, and comprehensive primary data from the baseline survey, 75/100,000/year. Using all four sources of preliminary data, we determined realistic anticipated outcomes for arm 2 to be 95/100,000/year and 206/100,000/year for arm 3 [11, 12, 14].

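### The year-1 primary test leaves out the factors that the trial minimizes on; if they are prognostic, it is inefficient and somewhat conservative

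*Protocol article*

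**What the plan says.** In the allocation section, "Fokontany characteristics that were likely to be associated to the primary outcome of TB detection rates were identified as potential confounders". The section names four: the TB notification rate in the year before the trial, distance to the nearest CDT, Fokontany population, and closest TB care center. They are split at the median, weighted 0.3, 0.3, 0.3 and 0.1, and "All these four factors will be included into the randomization algorithm". The same section calls them prognostic.

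In {20a}, "The primary analysis will compare notification rates between arms after 1 year", using a simple t-test and a "nonparametric Mann–Whitney *U* test weighed by Fokontany size with Fokontany as the unit of analysis". No covariate is named. The two-year mixed model has only arm, year and their interaction as fixed effects. Section {20b} uses the four factors for stratified reporting only. No reason is given for leaving them out of the primary comparison.

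**The concern.** A factor that is balanced by design because it predicts the outcome should normally also be in the analysis. Otherwise the variation it explains stays in the error term, and the standard error ignores the balance that minimization has produced. The test then loses power and tends to be conservative. Median splits also leave imbalance within each half of a continuous factor, which an unadjusted test does not correct.

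This trial has little slack. The arm 3 versus arm 2 test uses 32 clusters, the design power is 80%, and the interim analyses section {21b} says that the study counts as negative if year 1 shows no significant difference. Precision lost at that point can decide the trial's conclusion.

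**Working it through.** **Inputs, all from Sample size {14}:** "assuming a one-sided *α* = 0.05 test with 80% power"; "116% increase in TB case detection rate from 95/100,000/year to 206/100,000/year"; "intraclass correlation coefficient (ICC) of 0.0005 for sample size adjustment"; "average Fokontany cluster size of 1800 inhabitants"; 16 clusters per arm.

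**1. The plan's own figure reproduces.**
- Two-proportion normal formula, pooled variance under the null, p₁ = 0.00095, p₂ = 0.00206: 15,081 people per arm.
- Design effect: 1 + 1799 × 0.0005 = 1.8995.
- Clusters: 15,081 × 1.8995 / 1800 = 15.91, so 16 per arm, with 80.2% power.

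**2. Cluster-level version of the same test.**
- SD of a cluster rate = √[½(p₁(1−p₁) + p₂(1−p₂)) × 1.8995 / 1800] = 125.9 per 100,000.
- Noncentrality = 111 / (125.9 × √(2/16)) = 2.49.
- One-sided power of a t-test with 30 df: 78.6%.

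**3. How much a covariate can explain.** The between-cluster share of the variance is 0.8995 / 1.8995 = 47%. The rest is count noise that no cluster covariate can remove. The main covariate is noisy too: at the baseline survey rate of 75 per 100,000, a cluster of 1,800 has about 1.35 cases a year.

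**4. Power by formula.** Multiply the residual variance by (1 − R²), so that the noncentrality becomes 2.49/√(1 − R²), and spend 3 df (27 left):

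| R² | Power | Change from 78.6% |
|---|---|---|
| 0 | 78.4% | −0.2 |
| 0.10 | 82.0% | +3.4 |
| 0.20 | 85.8% | +7.2 |
| 0.25 | 87.7% | +9.1 |
| 0.35 | 91.4% | +12.8 |

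An R² of 0.20 to 0.35 means explaining 0.20/0.47 = 42% to 0.35/0.47 = 74% of all true between-cluster variation.

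**5. Power by simulation.** Poisson counts, ICC 0.0005, a noisy one-year baseline rate, minimization as planned, 4,000 runs per setting. The Monte Carlo standard error is about √(0.8 × 0.2/4000) = 0.6 points for power and √(0.05 × 0.95/4000) = 0.3 points under the null. Adjustment is for continuous covariates.

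| Association with outcome (approx. R²) | Power, unadjusted → adjusted | Change | Null rejection, unadjusted / adjusted |
|---|---|---|---|
| None | 81.0 → 79.3% | −1.7 | 5.1 / 5.0% |
| Weak (0.06) | 79.3 → 79.1% | −0.2 | 5.1 / 5.3% |
| Moderate (0.11) | 80.7 → 82.1% | +1.4 | 4.5 / 4.8% |
| Strong (0.19) | 81.2 → 85.2% | +4.0 | 4.5 / 5.4% |
| Perfectly stable risk (0.23) | 81.8 → 87.9% | +6.1 | 4.2 / 5.3% |
| Perfectly stable risk (0.30) | 81.8 → 89.6% | +7.8 | 3.8 / 5.0% |
| Perfectly stable risk (0.40) | 82.1 → 93.2% | +11.1 | 3.2 / 5.0% |

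The simulated gains are smaller than the formula's at the same R². The likely reasons are that minimization already recovers part of the precision, and that the formula leaves out the chance correlation between arm and covariates. Adjusting for the median-split factors gained less: +0.9, +2.2, +2.2, +3.7 and +5.5 points in the last five rows.

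**6. Sensitivity to the simulation model.** With constant ICC, and with distance and population given no effect, adjustment changed power by about +2 points (three covariates) to +4 (baseline rate only) at perfect stability, −1 to +1 when 60% of the rate persists, and −2 when baseline is uninformative. A more favorable set of assumptions with stable rates gave 80.5 → 87.0% at constant ICC and 64 → 76% at constant between-cluster CV. With only 60% of clusters keeping their rate, these fell to 80 → 82% and 63 → 66%.

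**The case against.** The strongest reply is that the planned test is valid, matches the sample-size method, and gains from minimization anyway. That stands: the simulated null rejection was at or below 5%, within Monte Carlo error. A reader might infer that the primary test is invalid or has inflated type I error; nothing in the documents or the calculations supports that.

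A reader might also infer that the plan gives away 7 to 12 points of power at no cost. The documents do not support this either. The article gives no R² and no baseline-to-outcome correlation, and gains of that size need nearly stable cluster rates or a very strong association. Stability is doubtful here. The baseline factor reflects passive, smear-based notification, while arms 2 and 3 add active case finding and Xpert Ultra, which may find more cases where access was poor. Eligibility also requires a confirmed case in the preceding 6 months, which selects on part of the baseline covariate. In a rough simulation with perfect stability, the gain was 80.0 → 84.5% without that selection and 84.6 → 87.0% with it. Nor is adjustment free: it uses degrees of freedom, and power falls if the covariates explain nothing.

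Population is not ignored, since it is the rate denominator and the test weight.

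Finally, a separate analysis plan may exist. But {20a} states an unadjusted primary test; it does not leave the choice open.

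**Conclusion.** The point holds as one of efficiency and consistency. The article treats four factors as prognostic, minimizes on them, and then specifies a primary test that adjusts for none of them. If they are prognostic, the test is inefficient and somewhat conservative: 3.2–4.5% under the null in the moderate to strongest simulated settings, against 4.8–5.4% after adjustment.

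The expected change in power from adjusting is about −2 to +8 points. The lower end is the case of no association. The upper end corresponds to a simulated R² of about 0.30 with perfectly stable cluster risk. It is not a strict bound, because one still more favorable setting gave +11. With weak to moderate association the change is about 0 to +1.4 points.

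This rests on the stated ICC of 0.0005 being the total, unadjusted between-cluster correlation, on the stated rates and cluster size, and on simulated associations that are assumptions. The changes in power refer to the t-test; the Mann–Whitney test was not simulated.

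**What to change.** Before year-1 data are analysed by arm, amend {20a} as follows.

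- **Primary analysis:** a size-weighted cluster-level linear regression of the year-1 rate in arms 2 and 3 on arm plus the minimization factors. Enter baseline rate, distance and population as continuous variables. Include closest TB care center, or state why it is omitted.
- **Report:** the adjusted rate difference with its confidence interval, and the R² assumed for any restated power.
- **Sensitivity analysis:** the unadjusted size-weighted t-test.

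If the arm comparison has already been seen at a 12-month review, the adjusted analysis can still be reported but must be labelled as specified afterwards.

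The cost is wording, plus about 3–4 degrees of freedom out of 30 (more if closest center has more than two categories). By formula that is 0.2–0.3 points of power; in simulation it is up to about 2 points if the covariates explain nothing. Minimization already requires these values for every cluster, so no new data are needed.

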**Methods:**

A cluster randomized controlled trial will be performed. Forty-eight rural village groups (or Fokontany) in the Vohibato district of Madagascar will be randomized to one of three interventions arms. Arm 1 (standard of care) involves healthcare facility-based passive case detection with smear microscopy testing. Arm 2 (best practice) consists of active case finding and Xpert MTB/RIF Ultra PCR testing followed by household contact investigations. Arm 3 (novel intervention) includes the same interventions as arm 2, with addition of sputum culture and *M. tuberculosis* whole genome sequencing for all newly diagnosed cases. In arm 3, molecular suggested putative outbreaks are investigated, and additional TB suspects are appropriately tested. The intervention observational period will be 2 years. The primary outcome will be the number of detected cases/100,000/year in each arm after 1 year of intervention.

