### Outcomes {12}

Globally, TB incidence is reported as number of cases/100,000 population/year. TB cases are defined by WHO as pulmonary or extra-pulmonary TB, adult or pediatric TB, and bacteriologically confirmed or non-confirmed TB. Within underdeveloped health systems, number of cases diagnosed by NTPs (case detection/100,000/year) is usually less than real incidence as estimated by WHO. Case detection/100,000/year is a standardized WHO indicator allowing comparisons between interventions. It is also the best available surrogate marker for impact on transmission and short- and long-term disease control. In this study alike, the primary outcome will be the difference in TB incidence (TB case detection/100,000/year) between arms 3 and 2 during the first year of the study intervention. Secondary outcomes will include the difference in TB incidence between arms 3 and 1 and between arms 2 and 1. Secondary outcomes will also include all the above incidence difference between arms during 2 years of intervention. For all primary and secondary outcomes, sub-group analyses based on biological sex, age, and baseline cluster characteristics will also be performed. Generally, an increase in TB detection is desirable since additionally diagnosed patients would otherwise go unnoticed, transmit, and either self-present to care at a later stage of disease or die. In this study, the objective will not be to accurately assess disease incidence but rather to measure the increase in the primary outcome between arms.

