### Interim analyses {21b}

Interim results will be analyzed every 12 months by the steering committee. If a statistically significant benefit is shown early in the study, results will be disseminated, and the study will be continued until interventions have been implemented for a 2-year period in all clusters to assess longer term impact on TB control (statistical methods for primary and secondary outcomes). If no significant difference between groups is seen after 1 year, this study will be considered negative. We will complete 2 years of intervention to further investigate transmission risk factors emerging from outbreak investigations and long-term impact on case detection rates.

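### For arm 3 versus arm 2 in year 1, the primary analysis contains two tests on two population denominators, and nothing says which result decides

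*Protocol article*

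**What the plan says.** **Contrast.** Outcomes {12} states that "the primary outcome will be the difference in TB incidence (TB case detection/100,000/year) between arms 3 and 2 during the first year", and then: "Secondary outcomes will include the difference in TB incidence between arms 3 and 1 and between arms 2 and 1". Sample size {14} agrees: "This study will be powered to demonstrate superiority of arm 3" over arm 2, "assuming a one-sided *α* = 0.05 test with 80% power", using a size-weighted t-test only.

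**Tests.** Statistical methods {20a} describes the primary analysis as a comparison of notification rates between arms "using a simple *t*-test and nonparametric Mann–Whitney *U* test weighed by Fokontany size with Fokontany as the unit of analysis". The two tests are joined by a plain conjunction. There is no order of precedence and no rule for a split result.

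**Denominators.** The same section says: "To estimate Fokontany size, we will use two approaches". One projects the 2019 census forward at 2.7% a year. The other takes the population that health authorities report when case-finding teams visit. Neither is labelled main or sensitivity.

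**Verdict.** Interim analyses {21b} says: "If no significant difference between groups is seen after 1 year, this study will be considered negative".

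**Abstract.** The Methods paragraph words the outcome per arm, without a contrast: "The primary outcome will be the number of detected cases/100,000/year in each arm after 1 year of intervention".

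**The concern.** A confirmatory claim at a stated error rate needs one deciding result, or a rule for combining several. Here the stated level belongs to a single t-test, but the analysis section produces four results for the same contrast (two tests on each of two denominators), and the verdict rule does not say which of them it refers to.

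The choice can matter. A cluster of 1,800 people expects 1,800 × 95/100,000 = 1.7 cases a year in arm 2 and 1,800 × 206/100,000 = 3.7 in arm 3. Counts this small are skewed and tied, so a mean-based and a rank-based test can fall on opposite sides of the threshold. The two tests also address different quantities, and only the t-test matches the rate difference and confidence interval that {20a} promises.

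The trial is open-label, and the visit-based denominator is collected after allocation. If the choice is still open when results are seen, it cannot later be shown to have been made independently of them.

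**Working it through.** **1. Reproduce the planned size.** Inputs from Sample size {14}: rates 95 and 206 per 100,000 per year, ICC 0.0005, 1,800 people per cluster, one-sided α = 0.05, power 80%.

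- Individuals per arm: n = (z₀.₉₅ + z₀.₈₀)² × [p₁(1−p₁) + p₂(1−p₂)] / (p₂−p₁)² = (1.645 + 0.842)² × 0.003005 / 0.00111² ≈ 15,078.
- Design effect: 1 + (1,800 − 1) × 0.0005 = 1.8995.
- Clusters per arm: 15,078 × 1.8995 / 1,800 = 15.91, so 16.

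The plan's figure reproduces. It describes one test, on one denominator, for one contrast. Power with 16 clusters per arm is 80.2% by normal approximation, or 78.6% using the t distribution with 30 degrees of freedom.

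**2. Count the candidate results.** 2 tests × 2 denominators = 4 p-values for arm 3 versus arm 2.

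**3. Simulate under no arm difference.** There were 20,000 trials per setting, with 16 clusters per arm.

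- From the protocol: ICC 0.0005 and mean cluster size 1,800. Counts were gamma-Poisson with between-cluster variance ICC × p(1−p). The common true rate was 95 or, as a variation not taken from the protocol, 150 per 100,000.
- Assumed, because the protocol does not give them: cluster-size CV 0.4, and an independent error of 5%, 15% or 25% in each denominator.
- Tests: a size-weighted t-test on 30 degrees of freedom, and a standard tie-corrected Mann–Whitney U. The U test was left unweighted because the protocol does not define the weighted form.
- Monte Carlo standard error near an 8% rate: √(0.08 × 0.92 / 20,000) ≈ 0.2 percentage points.

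Type I error for arm 3 versus arm 2, as ranges over the six settings:

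| Rule that declares a difference | One-sided 5% | Two-sided 5% |
|---|---|---|
| t-test, one denominator | 5.2–5.5% | 4.8–5.7% |
| t or U, one denominator | 6.8–7.4% | 7.0–7.5% |
| t-test, either denominator | 5.8–7.1% | 5.8–7.2% |
| either test, either denominator | 7.8–9.5% | 8.0–9.7% |
| t and U both, one denominator | 2.9–3.3% | 2.7–3.2% |

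A separate simulation with a size-weighted rank test (6,000 trials per setting, rate 95 per 100,000, denominator discrepancy 10–20%) gave 6.6–7.5% for either test and about 8% for all four results. The pattern therefore does not hinge on leaving the U test unweighted.

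**4. How often do the two tests split?** On one denominator, the split rate is (t or U) minus (t and U). One-sided, this is 3.7–4.2% of null trials across the settings. A further run of 4,000 trials per setting, on the same assumptions, gave about 3.5% under the null and about 12% at the design effect of 206 versus 95.

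**The case against.** The strongest reply is that the protocol already points to a lead result. The t-test is the only test in the sample size, it comes first in {20a}, and it matches the reported rate difference. The census projection is also listed before the visit-based count. On that view the U test and the second denominator are robustness checks, and the statistical analysis plan, which is not shown, may say so. This has some force: it shows which choice the authors probably intend. It does not settle the point, because {20a} places both tests under the primary analysis and no sentence says that the t-test or the census figure decides. The protocol is not silent here. It states two primary tests and a trial-level verdict rule that do not fit together.

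Three stronger readings should be resisted.

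- **The arm pair is open.** A reader might infer this from the loose wording in {20a}, {21b} and the abstract. Outcomes {12} makes arm 3 versus arm 2 primary and the other pairs secondary, and Sample size {14} powers that contrast. Error rates that count all three pairs therefore do not describe this protocol.
- **Any significant result makes the trial positive.** Section {21b} says only when the trial is negative. The converse is not written, and requiring both tests to agree is equally compatible with the text; that rule would be conservative.
- **The tests often disagree.** Under the null they split in about 4% of trials. The 12% at the design effect is roughly one trial in eight: enough to matter, but not frequent.

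**Conclusion.** The point holds for arm 3 versus arm 2 in year 1. Two primary tests and two denominators are specified without precedence, and the verdict rule does not identify the deciding result. The one-sided 5% level in Sample size {14} therefore does not describe the analysis as written. Depending on the unstated rule, the actual level lies between about 3% (both tests required) and about 8–10% (any of four results), with about 7% for either test on one denominator.

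The four-result figure depends on the assumed cluster-size CV of 0.4 and denominator errors of 5–25%; smaller denominator errors give the lower end. The inflation is moderate, and the sample size calculation itself is sound for the single t-test. What is at fault is the missing designation.

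**What to change.** - In {20a}, name one confirmatory test: the size-weighted t-test of arm 3 versus arm 2 over the first year, on one pre-named denominator. The census projection is a natural candidate because it does not depend on visits made after allocation. State the side and level of the test as well, since the sample size is one-sided at 5% while {20a} reports 95% intervals.
- Label the Mann–Whitney test and the other denominator as sensitivity analyses.
- Reword the verdict rule in {21b} so that it refers to that test and that contrast.
- Align the wording of {20a} and the abstract with Outcomes {12}.
- Date the change before arm-level first-year results are examined. If they have already been seen, say so and report all four results.

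The cost is wording, plus giving up the freedom to quote the more favourable result. Simulated type I error returns to about 5% (4.8–5.7% over all settings), and 16 clusters per arm with roughly 80% power is unchanged.

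### The trial is sized on a one-sided 5% test, but the primary analysis and the verdict rule state no side and the results carry 95% CIs; read two-sided, the 80% power is about 67–70%

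*Protocol article*

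**What the plan says.** Three sections of the protocol article bear on this.

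- **Sample size {14}.** The aim is directional: "This study will be powered to demonstrate superiority of arm 3 “novel intervention” over arm 2 “best practice” after 1 year". The calculation proceeds "assuming a one-sided *α* = 0.05 test with 80% power". The ground for one side is that arm 3 only adds to arm 2, so "it is assumed it cannot be inferior". The other inputs are a "116% increase in TB case detection rate from 95/100,000/year to 206/100,000/year", an "intraclass correlation coefficient (ICC) of 0.0005 for sample size adjustment", and 1800 inhabitants per Fokontany. The result is 16 Fokontany per arm.
- **Statistical methods for primary and secondary outcomes {20a}.** The 1-year comparison uses a t-test and a Mann–Whitney test, both weighted by Fokontany size. No side is given. Then: "Detection rate differences and 95% confidence intervals (CI) will be reported".
- **Interim analyses {21b}.** "If no significant difference between groups is seen after 1 year, this study will be considered negative". No side is given here either, although the sentence before it speaks of a significant benefit, which is directional.

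Nowhere does the article mention a 90% CI or a one-sided bound, or say how the one-sided test relates to the 95% CI.

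**The concern.** A one-sided 5% test matches a two-sided 90% CI or a one-sided 95% lower bound. A 95% CI for a difference, in its usual two-sided sense, matches a one-sided 2.5% test. The article therefore fixes one threshold for sizing and displays an interval that belongs to another. Its positive-or-negative rule is worded so that either could be applied.

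The consequence is practical. If the one-sided p-value for arm 3 over arm 2 falls between 0.025 and 0.05, the trial succeeds by the criterion it was sized on, while the published 95% CI includes zero. With no stated rule for which governs, the choice could be made after the data are seen. It also changes the power: 80% belongs to the more lenient criterion only.

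**Working it through.** **Inputs, all from Sample size {14}:** p1 = 0.00095 (arm 2), p2 = 0.00206 (arm 3), ICC = 0.0005, cluster size m = 1800, 16 clusters per arm, one-sided α = 0.05, power 80%. The article prints no formula, so the standard two-proportion calculation with a design effect was used.

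**Step 1. Reproduce the planned 16.**
- Design effect: 1 + (1800 − 1) × 0.0005 = 1.8995.
- Variance sum: 0.00095 × 0.99905 + 0.00206 × 0.99794 = 0.0030049.
- Squared difference: 0.00111² = 1.2321 × 10⁻⁶.
- One-sided 0.05: (1.645 + 0.842)² = 6.183; n = 15,078 persons per arm; 15,078 × 1.8995 / 1800 = 15.9, rounded up to **16**.
- Two-sided 0.05: (1.960 + 0.842)² = 7.849; n = 19,142; 19,142 × 1.8995 / 1800 = 20.2, rounded up to 21.

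The other variants tried do not give 16 either: one-sided with continuity correction gives 18, and one-sided with one cluster added for small numbers gives 17. The one-sided choice therefore determines the size of the trial.

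**Step 2. Power with 16 per arm under each criterion.**
- Standard error of the difference: √(0.0030049 × 1.8995 / (16 × 1800)) = 0.000445, or 44.5 per 100,000.
- Standardised effect: 111 / 44.5 = 2.493.
- Normal approximation: Φ(2.493 − 1.645) = 80.2% one-sided; Φ(2.493 − 1.960) = 70.3% for the 95% CI to lie above zero.

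| Criterion | Normal | t, 30 df | Simulation |
|---|---|---|---|
| One-sided 0.05 | 80.2% | 78.6% | 80.1% |
| 95% CI above zero | 70.3% | 67.5% | 69.3% |
| Gap | 9.9 | 11.1 | 10.8 |

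The simulation drew beta-binomial counts in equal-sized clusters, with an unweighted t-test and 40,000 runs.

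**Step 3. The band in which the two criteria disagree.** At the planned standard error and 30 df, the one-sided test is significant above about 1.70 × 44.5 = 76 per 100,000. The 95% CI excludes zero only above about 2.04 × 44.5 = 91 per 100,000. An observed difference between these values is positive by one reading and not by the other.

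**The case against.** The strongest reply is that the side is specified once, in {14}, for the same t-test on the same 1-year comparison that {20a} names. On that reading the 95% CI is only an estimation summary, because {20a} says it is reported and does not say it decides. The significant-benefit wording in {21b} points the same way. A condensed article may also leave this detail to an analysis plan that is not shown.

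Much of this stands. The 80% is not miscalculated, and reporting a 95% CI is not wrong in itself. That the interval is two-sided is an inference from normal usage. What the reply does not remove is that the verdict sentence itself, "If no significant difference between groups is seen after 1 year, this study will be considered negative", is non-directional, while the article has fixed an error rate, an interval and a binary rule that do not fit together as written. This is more than detail left for later.

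A reader might also infer that the one-sided test is invalid because, with no true effect, the observed arm 3 rate would fall below arm 2 about half the time. That does not follow. "Given the purely incremental nature of arm 3 “novel intervention,” it is assumed it cannot be inferior" is an assumption about the true effect, which chance variation in the estimate does not contradict. The test still holds its stated 5% error rate. Whether 0.05 or 0.025 one-sided is preferable is a judgement, and the article declares its choice openly.

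**Conclusion.** The point holds as an unreconciled decision rule. The stated 80% is right for the one-sided 0.05 test (about 79–80% with 16 per arm). It does not carry over to a two-sided analysis or to a reading from the 95% CI, where power is about 67–70%. At the planned effect, about 10–11% of trials would fall between the two criteria, and the article does not say which governs.

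A reader might infer that the power calculation is wrong or that clusters must be added. The documents support neither: the calculation reproduces, and the gap can be closed by wording.

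The figures rest on the article's planned rates and ICC, a two-sided reading of the 95% CI, and equal cluster sizes; unequal sizes would lower both sets of power figures. Severity is moderate. The rule governs the primary verdict, so it should be settled before the 1-year outcomes are analysed.

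**What to change.** State one decision rule, in the same terms, in {14}, {20a} and {21b}. Either of two options is coherent:

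1. **Keep the one-sided 0.05 test.** Say so in {20a} and {21b}, name the two-sided 90% CI or the one-sided 95% lower bound for arm 3 minus arm 2 as the decision interval, and label the 95% CI as descriptive. The 80% stays. This costs a sentence in each section.
2. **Make the two-sided 95% CI decisive.** Say so in all three sections and restate power with 16 per arm as about 67–70%. This tightens the declared error rate and gives a less favourable power figure.

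Under either option, word the negative verdict in {21b} to match the chosen test. The non-inferiority assumption in {14} may stay as the stated reason for option 1.

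No extra clusters are needed. Restoring 80% under option 2 by enlargement would take 21 per arm (normal) or 22 (t-test). That is 63 to 66 Fokontany in three equal arms, more than the 56 that the Eligibility criteria section counts as eligible.
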